#### Missing data

Missing observations will be presented as a percentage of the total. For the assessment of the primary outcome measure, a drop-out is defined as a lesion not followed up to the 12 months + / − 45 days mark. In the case of the death of a patient before the 12 months assessment, only lesions that had progressed will be regarded as not having achieved tumour control at 12 months and lesions where progression could not be determined before the death of the patient will be regarded as a drop-out. A sensitivity analysis will be done to assess potential bias due to drop-outs before the 1-year assessment. Depending on the differences between the primary analysis and the sensitivity analysis, a tipping-point analysis may be performed.

The statistical analysis will be done using R Studio version 4.4.

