**Methods:**

Eligible patients are adults with up to 9 local treatment naïve CRLM of ≤ 3 cm completely treatable with either MWA alone or MWA with resection and/or radiotherapy within 8 weeks. Data are collected, at baseline, every 3 months until 12 months, and thereafter every 6 months until the end of the study. The primary outcome measure is local tumour control. Secondary outcome measures are overall survival, (hepatic-) disease-free survival, time-to-progression untreatable by ablation, systemic therapy vacation, safety, and quality of life. Covariates related to the primary outcome measure will be assessed using a stratified log-rank test and an univariable Cox proportional hazard regression. A sample size of 500 patients with 750 lesions produces a two-sided 95% confidence interval with a precision equal to 0.057.

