### Primary outcome measure

The primary outcome measure is the local control rate for all ablated tumours at 1 year (defined as fully ablated with no evidence of disease within the ablation zone at 12 months + / − 45 days after the last ablation of the respective tumour) as assessed by the investigatorsʼ routine protocols (Table 2).

**Table 2 Tab2:** Primary and secondary outcome measures

	Outcome measure	Measured according to	Definition
*Primary outcome measure*			
Effectiveness	Local tumour control at 12 months on a per lesion basis	Investigator assessment	Tumour is considered to be fully ablated with no evidence of disease within the ablation zone at 12 months + / − 45 days after the last ablation
*Secondary outcome measures*			
Safety	Adverse events	CTCAE V5.0	
Effectiveness	Overall survival	Investigator assessment	Time between the first treatment and the time of death of any cause
	Overall disease-free survival	Investigator assessment	Time between the first treatment and the time of any progression, new tumours, or death
	Hepatic disease-free survival	Investigator assessment	Time between the first treatment and the time of any progression of hepatic tumours, new hepatic tumours or death
	Time to untreatable progression by thermal ablation	Investigator assessment	Time between the first treatment and the time of progression of a treated tumour that has been determined as not treatable by thermal ablation
	Systemic cancer therapy vacation	Investigator assessment	Time between the first treatment and the start of systemic cancer therapy
	Quality of Life	EORTC QLQ-C30	

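### For patients who die before 12 months, failure is defined more narrowly than in the primary outcome, so a known incomplete ablation becomes a drop-out

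*Protocol article*

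**What the plan says.** The Primary outcome measure section gives local control two parts. A controlled tumour is "defined as fully ablated with no evidence of disease within the ablation zone at 12 months", give or take 45 days, counted from the last ablation of that tumour. Table 2 repeats this per lesion: "Tumour is considered to be fully ablated with no evidence of disease within the ablation zone at 12 months + / − 45 days after the last ablation".

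The Missing data section gives a general rule, under which "a drop-out is defined as a lesion not followed up to the 12 months + / − 45 days mark". It then gives a rule for patients who die before the 12-month assessment. Its failure branch reads: "only lesions that had progressed will be regarded as not having achieved tumour control at 12 months". A second branch of the same rule names the drop-outs among these patients: "lesions where progression could not be determined before the death of the patient will be regarded as a drop-out". The section adds: "A sensitivity analysis will be done to assess potential bias due to drop-outs before the 1-year assessment". A tipping-point analysis may follow, depending on the result. The method of the sensitivity analysis is not described.

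**The concern.** The two sections use different ideas of failure. Under the primary definition a tumour can fail without growing, because it is enough that it was not fully ablated. Under the death rule, progression is the sole route to failure. A lesion with residual tumour on record after its last ablation, in a patient who dies before any progression is seen, fails by the first rule but not by the second.

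At stake is the headline per-lesion control rate. A lesion already known to have failed would be handled as missing. Every such lesion is a failure, so leaving it out can move the rate only upward.

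**Working it through.** **Step 1. Compare the two rules.**

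| Last documented local status | Primary definition | Rule for death before 12 months |
|---|---|---|
| Progressed | Failure | Failure |
| Residual after last ablation, not progressed | Failure | Not a failure; drop-out under the general definition |
| Unknown | Cannot be classified | Drop-out |

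The rules disagree only in the second row. The death-specific drop-out clause covers lesions whose progression could not be determined, so it does not clearly take a residual lesion known not to have progressed. The general definition does, because the lesion was not followed to the 12-month window.

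**Step 2. Reproduce the plan's own figure.** The Sample size calculation section states a precision of 0.057 for 500 patients with 1.5 tumours each (750 lesions) at a proportion of 0.8. The Wilson interval has

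- centre = (p + z²/2n) / (1 + z²/n)
- half-width = z·√(p(1−p)/n + z²/4n²) / (1 + z²/n)

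With n = 750, p = 0.8 and z = 1.96 it runs from 0.7699 to 0.8271. The full width is 0.0572, which matches. This figure is not in dispute and only sets a scale. At the 976 lesions reported under Current status of the study, the half-width at 0.8 is 0.0251, or 2.5 points.

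**Step 3. Size of the bias, simple case.** Let S be the controlled lesions, D the denominator under the literal rule and R the known residual, non-progressed lesions in early deaths. The literal rate is S/D and the consistent rate is S/(D + R), so the literal rate is higher whenever R > 0. This takes drop-outs as leaving the denominator, which the article implies but does not state.

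The documents give neither the share of lesions in early deaths nor the share of those incompletely ablated. Assume 10% and 5% to 10%, with 80% control in the remaining lesions. Progressed lesions in early deaths are ignored here.

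- Lesions in early deaths: 0.10 × 976 ≈ 98, leaving D = 878
- S = 0.80 × 878 ≈ 702, literal rate 702/878 = 79.95%
- R = 0.05 × 98 ≈ 5: 702/883 = 79.50%, a difference of 0.45 points
- R = 0.10 × 98 ≈ 10: 702/888 = 79.05%, a difference of 0.90 points

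**Step 4. Allow for progressed lesions in early deaths, and widen the range.** Let A be the lesions of patients alive at 12 months and P the progressed lesions in early deaths, assumed to be 20% of early-death lesions. Compare 0.8A/(A + P) with 0.8A/(A + P + R). For 10% early-death lesions and 10% residual: A = 878.4, P = 19.5, R = 9.8. The rates are 702.7/897.9 = 78.26% and 702.7/907.7 = 77.42%, a difference of 0.84 points.

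Overstatement in percentage points:

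| Lesions in early deaths | Residual 2% | 5% | 10% | 20% |
|---|---|---|---|---|
| 5% | 0.08 | 0.21 | 0.41 | 0.82 |
| 10% | 0.17 | 0.42 | 0.84 | 1.67 |
| 15% | 0.26 | 0.65 | 1.30 | 2.55 |

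Between about 1 and 29 lesions change class across this grid. For 10% early-death lesions and 5% to 10% residual, the two calculations together give about 0.4 to 0.9 points.

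**The case against.** The affected group is small. A lesion must be residual after its last ablation, not progressed, and in a patient who dies before 12 months. Table 1 limits the largest treated lesion to 3 cm, requires an intention to treat all visible disease completely and excludes a life expectancy below 6 months. The clock runs from the last ablation, so a residual tumour that is later fully re-ablated and clear at 12 months counts as controlled. In a living patient assessed at 12 months, residual tumour is a failure in any case. All of this stands, and it limits the size of the effect.

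It can also be said that the article does not define progression, so investigators might record residual tumour as progression. They might, but the 36 activated centres could then differ, and nothing in the text asks for it. The planned sensitivity analysis offers partial protection. It would still treat a known outcome as missing, and the headline rate would still follow the literal rule.

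A reader might go further and infer that incomplete ablations stay event-free in the analysis of factors for local control, since the abstract says "Covariates related to the primary outcome measure will be assessed using a stratified log-rank test and an univariable Cox proportional hazard regression". The document does not support this. The events in the Time-to-event section belong to the secondary outcomes, and for the disease-free endpoints they include new tumours and death as well as progression. That section gives a starting point for per-lesion analyses but no local-control event, and the Outcome measures section gives none either. The article is silent on that event. It does not state one that leaves out incomplete ablation, and a full protocol or analysis plan commonly supplies it.

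**Conclusion.** The point holds for the death rule. As written, that rule is narrower than the primary definition, and read literally it turns a documented failure into missing data. The direction is certain wherever such a lesion exists: control is overstated. The size rests on assumed rates. It is about 0.4 to 0.9 points around 80% for 10% early-death lesions with 5% to 10% of them residual, and 0.08 to 2.55 points over the wider grid. The central range is below the standard error of about 1.35 points, √(0.8 × 0.2/878), and below the 2.5-point Wilson half-width. The effect is limited to early deaths and is probably small. It deserves correction because it contradicts the definition of the primary outcome, not because it is likely to change the study's conclusion.

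**What to change.** In the Missing data section, widen the failure clause for patients who die before the 12-month assessment. It should cover lesions that progressed and lesions documented as not fully ablated after their last ablation, without the restriction to progression alone. In the same sentence, reserve the drop-out category for lesions whose local status was unknown at death.

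The change is one phrase and needs no new data, because the primary outcome already requires the completeness of ablation to be recorded. It can be made before the final analysis, as follow-up runs to January 2026. The downside is that the reported control rate may be slightly lower.

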### Statistical analysis

#### Sample size calculation

As the total number of available lesions will depend on how many lesions per patient are treated, several scenarios were used to calculate the required sample size to achieve sufficient precision for analysis. Based on previously published data [11, 16], local tumour control rates of 60%, 70%, and 80% for 1, 1.5, and 2 tumours per patient were chosen as possible scenarios. Using the resulting sample size, the expected precisions were calculated using the two-sided 95% confidence interval according to the Wilson score method [20, 21].

A sample size of 500 patients with a median of 1.5 tumours per patient produces a two-sided 95% confidence interval with a precision equal to 0.057 when the sample proportion is 0.8.

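### The drop-out and death rules make a lesion's inclusion in the primary 12-month local control rate depend on its outcome, which biases the rate by roughly half a point to 3 points under plausible assumptions

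*Protocol article*

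**What the plan says.** The Primary outcome measure section sets a per-lesion proportion: "The primary outcome measure is the local control rate for all ablated tumours at 1 year". Table 2 gives the criterion for success: "Tumour is considered to be fully ablated with no evidence of disease within the ablation zone at 12 months", with a 45-day window either side. The clock starts at the last ablation of the tumour concerned.

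The Missing data section decides which lesions count:

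- **General rule:** "a drop-out is defined as a lesion not followed up to the 12 months" (same window). No exception is made for a lesion already seen to have progressed.
- **Death before the assessment, progressed lesions:** "only lesions that had progressed will be regarded as not having achieved tumour control at 12 months".
- **Death before the assessment, other lesions:** "lesions where progression could not be determined before the death of the patient will be regarded as a drop-out".
- **Safeguards:** "A sensitivity analysis will be done to assess potential bias due to drop-outs before the 1-year assessment". Beyond that, depending on how the two analyses differ, "a tipping-point analysis may be performed".

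**The concern.** An evaluable-only proportion is sound if being evaluable is unrelated to outcome. Here the rule itself creates a relation.

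In patients who die early, a progressed lesion stays in as a failure. A lesion with no progression found cannot meet the 12-month criterion and becomes a drop-out. The retained lesions of deceased patients are therefore all failures, which pulls the rate down.

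In patients lost alive, the text does not classify a lesion that progressed before the loss. Read literally it is a drop-out, so a known failure vanishes, although the same lesion followed by death would be counted. If loss is more likely after progression, this pushes the rate up.

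The study tests no confirmatory hypothesis. Its main product is a precise estimate of this rate, and a larger number of lesions does not reduce this kind of error.

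**Working it through.** **1. The plan's own precision.** Full width of the 95% Wilson interval: 2z/(1+z²/n) × √[p(1−p)/n + z²/(4n²)], with z = 1.96 and p = 0.8 (Sample size calculation).

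- n = 500 × 1.5 = 750: width 0.0572, which reproduces the stated 0.057; half-width 2.9 points.
- n = 976 (Current status of the study): width 0.0501; half-width 2.5 points.

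Both treat lesions as independent.

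**2. Inputs for the bias.** True (net) control S = 0.80 is one of the planning values: "local tumour control rates of 60%, 70%, and 80% for 1, 1.5, and 2 tumours per patient were chosen as possible scenarios". The 12-month probabilities of death (d) and loss (c) are not in the article and are assumed. Times to progression, death and loss are taken as exponential, with hazards −ln S, −ln(1−d) and −ln(1−c). Drop-outs are taken to leave the denominator. Re-ablation is not modelled.

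- Reading A: a lesion that progressed before its patient was lost counts as a failure.
- Reading B (literal): that lesion is a drop-out.

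The death rule is the same under both.

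**3. Death alone (d = 10%, c = 0).**

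- Alive and controlled: 0.80 × 0.90 = 0.720.
- Progression before death: 0.2231/(0.2231 + 0.1054) × (1 − 0.720) = 0.190.
- Rate under the rule: 0.720/(0.720 + 0.190) = 79.1%.
- References: net control 80.0%; 1 minus cumulative incidence with death competing, 1 − 0.190 = 81.0%.

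The rule matches neither, and it does not match the 72% alive and controlled.

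**4. Death and loss, both unrelated to progression.** Let E = S(1−d)(1−c) be the lesions controlled and followed to 12 months, F = [hazard of progression / sum of the three hazards] × (1 − E) the documented failures, and K = (1−S)(1−d)(1−c) the failures with complete follow-up. Reading A gives E/(E + F). Reading B gives E/(E + K + w(F − K)), where w is the death hazard divided by the sum of the death and loss hazards.

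| d / c | E | F | K | A | B | 1 − cumulative incidence |
|---|---|---|---|---|---|---|
| 5% / 5% | 0.722 | 0.190 | 0.181 | 79.1% | 79.6% | 80.5% |
| 10% / 10% | 0.648 | 0.181 | 0.162 | 78.2% | 79.1% | 81.0% |
| 10% / 20% | 0.576 | 0.172 | 0.144 | 77.1% | 79.0% | 81.0% |

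Against net control of 80% the shortfall is 0.4 to 2.9 points, or about half a point to 3 points. Against the competing-risk value it is 0.9 to 3.9 points. A simulation of 4,000,000 lesions per scenario agrees to within 0.03 points.

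**5. Loss more likely after progression (simulation, net control 80%).**

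| d / c | Loss hazard after progression | A | B |
|---|---|---|---|
| 10% / 10% | ×3 | 78.2% | 80.8% |
| 5% / 10% | ×3 | 78.7% | 81.2% |
| 5% / 20% | ×3 (death ×2) | 77.6% | 82.8% |
| 10% / 10% | ×2 (death ×2) | 78.2% | 79.9% |

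Reading A stays low. Reading B turns upward by about 1 to 3 points in the first three rows; in the fourth the two biases nearly cancel. An extreme case (10% death, 20% loss, ×5) takes B to about 85%.

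**The case against.** **A safeguard is already committed.** The sensitivity analysis for drop-out bias is unconditional; only the tipping-point step is optional. Its method may properly sit in the analysis plan. This stands, and it lowers the severity. It can expose the bias, but the headline figure keeps it.

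**The rate need not be biased on every reading.** A reader might infer that no reading escapes bias, and the article does not support that. The phrase about undeterminable progression could mean indeterminate imaging only. Lesions clear at the last scan before death would then count as controlled, and the rate with 10% death and no loss would equal the competing-risk value of 81.0%. That reading fits poorly with the 12-month criterion in Table 2 and with the general drop-out definition, but it is arguable. Under the literal reading, opposing biases can also nearly cancel.

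**The rules do not strictly contradict each other.** They are a general definition and a special rule for death. The fault is the unequal treatment of the same known failure and the silence on lesions that progressed before loss.

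**The size rests on assumptions.** A reader might also infer a bias as wide as the confidence interval. The figures do not support this: the full width is 5.0 to 5.7 points, while the usual bias is 0.5 to 3. Table 1 excludes patients with a life expectancy below 6 months, so early deaths may be few.

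**A remedy must not change the endpoint.** Counting first local progression as final failure would turn a re-ablated and later controlled tumour into a failure, contrary to the clock from the last ablation. This stands and shapes the fix.

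**Conclusion.** The point holds in a limited form. On the natural reading, the death rule admits lesions of deceased patients only as failures, and the literal drop-out definition discards known failures in patients lost alive. These are faults in stated rules, not details left to an analysis plan.

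The size depends on assumed death and loss rates, exponential times, removal of drop-outs from the denominator, and no re-ablation. At 80% net control, with 5–10% death and 5–20% loss, the rate is about 0.5 to 3 points low when loss is unrelated to progression. The literal rule can be about 1 to 3 points high when loss follows progression, and more in extreme cases. That is around or below the planned half-width. In a descriptive registry with a committed sensitivity analysis, this is a should-fix point.

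**What to change.** Apply one rule to death and loss in the primary analysis.

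- Count every documented local failure by 12 months as a failure, whatever happens to the patient afterwards. Keep the published definition: the clock runs from the last ablation of the respective tumour, so a re-ablated lesion is judged from that ablation. The Time-to-event section starts its per-lesion analyses at the first ablation, so the primary analysis needs its own stated clock.
- Let lesions without failure contribute follow-up to the last liver imaging.
- Estimate 12-month control as 1 minus the cumulative incidence of local failure with death as a competing event, or by Kaplan–Meier. State which estimand is meant, because the two differ (81.0% and 80.0% in step 3). Use a patient-clustered confidence interval.
- Keep the evaluable-only proportion as a sensitivity analysis, and make the tipping-point analysis unconditional, because the new estimator still assumes that loss before failure is uninformative.

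The cost is a change of wording and a little more analysis code, using data already being collected. The primary estimate would no longer be a simple proportion.

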## Current status of the study

Between October 2018 and June 2022, 100 hospitals that met the selection criteria were invited, of which 36 were activated (by means of training, access to the database, and eligibility to include patients). As of January 2023, 500 patients have been enrolled with 976 treated tumours, achieving the minimum sample size of 976 lesions for a precision between 0.04 and 0.06. Follow-up data will be collected until January 2026. The final clinical outcome results are expected to be published by 2027.

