## Discussion

CIEMAR is a Europe-wide, prospective multicentre observational study of patients with colorectal liver metastases treated with microwave ablation as standard therapy. Its primary outcome measure is to evaluate local tumour control, with secondary outcome measures being overall survival, (hepatic) disease-free survival, time to progression untreatable by thermal ablation, systemic cancer therapy vacation, safety and quality of life.

The robust data of real-world, 1-year tumour control per lesion will be used to determine factors that impact the effectiveness of MWA and to identify unresectable lesions that may still be optimal for MWA, thus potentially improving the curative approach to CRLM. While the level of evidence of observational data is considered low compared to randomised controlled trials (RCTs), several comparative studies have shown that outcomes of RCTs and observational studies are comparable in terms of treatment effect and quality [22–24]. Nevertheless, a recent meta-analysis showed that the risk of bias was directly correlated with the effect estimate [25]. Therefore, the choice of a robust primary outcome measure, inclusion criteria, and prospective data collection are essential in reducing the risk of bias [26–28]. In this study, the choice of a primary outcome measure appropriate for localised treatments allows CIEMAR to precisely evaluate the extent of local tumour control with MWA and relate this to its secondary effectiveness outcome measures (26). Hence, CIEMAR will combine the strengths of the observational design with the localised effects of interventional oncological treatments and thus be able to avoid the pitfalls of observational studies that focus on more general outcome measures, such as OS or progression-free survival.

Initially, CIEMAR aimed to include 700 patients with 1050 lesions with a precision of 0.05. Unfortunately, due to the COVID-19 pandemic, some centres were understaffed or even closed, while in other cases, resources had to be re-allocated to cope with the influx of COVID-19 patients and cancer treatments, including ablation treatments, were postponed or aborted. This had a negative impact on patient enrolment. Nevertheless, the current sample size of a minimum of 803 lesions with a precision of 0.04–0.07 is statistically sufficient to evaluate the primary outcome measure.

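### Two underived and conflicting minimum lesion numbers (976 and 803) are quoted with a best-case precision of 0.04 that the stated 60–80% control rates do not reach

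*Protocol article*

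**What the plan says.** The Sample size calculation section sets the method, a "two-sided 95% confidence interval according to the Wilson score method", and the scenarios: "local tumour control rates of 60%, 70%, and 80% for 1, 1.5, and 2 tumours per patient were chosen as possible scenarios". Its worked result begins "A sample size of 500 patients with a median of 1.5 tumours per patient produces" and continues to a "two-sided 95% confidence interval with a precision equal to 0.057 when the sample proportion is 0.8". The abstract gives the same result in lesions: "A sample size of 500 patients with 750 lesions produces a two-sided 95% confidence interval with a precision equal to 0.057".

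Two later sections give other numbers for the same 500-patient study:

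- Current status of the study: 976 tumours treated, "achieving the minimum sample size of 976 lesions for a precision between 0.04 and 0.06".
- Discussion: the initial aim was 700 patients with 1050 lesions and a precision of 0.05. After describing the effect of COVID-19 on enrolment, the text says that "the current sample size of a minimum of 803 lesions with a precision of 0.04–0.07 is statistically sufficient" for the primary outcome measure.

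The abstract's Results give the lesion count as at least 976. The Missing data section defines a lesion not followed to the 12-month window as a drop-out. It treats lesions of undetermined status in patients who die earlier in the same way.

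**The concern.** A reader who asks how many lesions the study needed finds 976 in one section and 803 in another, each called a minimum, and can derive neither. Because 976 is also the count accrued, the statement that the minimum was achieved cannot be checked against anything fixed beforehand.

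Both numbers come with a lower precision limit of 0.04. That is better than the 0.05 given for the original, larger design, although the reduced study has fewer lesions than the 1050 first intended. The Discussion cites its range when it calls the reduced size sufficient, so the range should follow from the method stated in the article.

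**Working it through.** **Inputs, all from the protocol article.** Two-sided 95% Wilson interval (z = 1.96); control rates p of 0.6, 0.7 and 0.8; 1, 1.5 or 2 tumours per patient, hence 500, 750 or 1000 lesions for 500 patients. The article combines 1.5 tumours with 80%, so the rates and the tumour numbers are crossed, not paired. Lesions are treated as independent, as in the article's own calculation.

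**Formula.** Full width = 2z·√[p(1−p)/n + z²/(4n²)] / (1 + z²/n).

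**Step 1: what precision means.** For n = 750 and p = 0.8:

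- p(1−p)/n = 0.16/750 = 0.0002133 and z²/(4n²) = 0.0000017; the root of the sum is 0.014664
- width = 2 × 1.96 × 0.014664 / 1.00512 = 0.0572

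The stated 0.057 reproduces. For n = 1050 and p = 0.8 the width is 0.0483, which agrees with the stated 0.05. Precision is therefore the full width. As a half-width, 0.057 would need only about 188 lesions.

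**Step 2: the two disputed ranges.**

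| Lesions | p = 0.6 | p = 0.7 | p = 0.8 | Article states |
|---|---|---|---|---|
| 750 | 0.0700 | 0.0655 | 0.0572 | 0.057 at 0.8 |
| 803 | 0.0676 | 0.0633 | 0.0553 | 0.04–0.07 |
| 976 | 0.0614 | 0.0574 | 0.0501 | 0.04–0.06 |
| 1000 | 0.0606 | 0.0567 | 0.0495 | – |

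The upper ends (0.07 for 803, 0.06 for 976) reproduce. The lower ends do not. The best of the 500-patient scenarios, 1000 lesions at 80%, gives 0.0495.

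**Step 3: what 0.04 would take.** At 80% control, a width of 0.040 needs 1,535 lesions. A width that merely rounds to 0.04 (below 0.045) needs about 1,213. With the lesion numbers held fixed, rounding to 0.04 needs a control rate of about 85% for 976 and 88% for 803. A single upper rate of 90% fits both: 0.0377 for 976 and 0.0416 for 803.

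**Step 4: other readings of the calculation.** At 60–80% control, Wald, continuity-corrected Wilson and Clopper-Pearson widths also stay at or above 0.050 (976) and 0.055 (803). Half-widths are 0.025–0.031 and 0.028–0.034, outside both ranges. A 90% interval gives 0.042 for 976 at 80%, but then 0.052 at 60%, which misses the stated upper end; the article also specifies 95%.

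**Step 5: drop-outs.** The article gives no drop-out rate. Assume, for illustration only, that 10–30% of the 976 lesions are not evaluable, which leaves 878 to 683. The width is then 0.053–0.060 at 80% control and 0.065–0.073 at 60%.

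**The case against.** Several points in the article's favour stand.

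- **A third minimum.** A reader might count 750 as another minimum. The article never calls it that; it is the planning example. There are two stated minima and one planning figure.
- **Sufficiency.** A reader might infer that the claim of sufficiency rests on wrong figures and so falls. It does not. The worst-case ends, which matter most for adequacy, are correct. At 80% control both 803 lesions (0.055) and 976 (0.050) improve on the planned 0.057.
- **A moved target.** It is tempting to say that the target was set to match accrual, or that these figures were used to justify the cut from 700 to 500 patients. The article attributes the shortfall to COVID-19 and only then remarks that the size suffices. The abstract's phrase for the count, at least 976, and the Discussion's reference to the current sample size both allow a looser reading as lower bounds on a count. The wording is poor, but no motive can be read from it.
- **What 803 counts.** It is 82% of 976 (803/976 = 0.823) and might be a count of evaluable lesions. The article does not say, so the figure should not be assumed wrong.
- **An unlisted scenario.** Both ranges fit control rates of 60–90%, which suggests an omitted scenario and not a miscalculation. That is plausible but an inference. If it is right, the omission is what needs correcting.
- **Drop-outs.** The Missing data section defines drop-outs and plans a sensitivity analysis. It does not state in so many words that they leave the primary analysis, although that is the natural reading.

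The practical consequence is also limited: enrolment is complete, no confirmatory hypothesis is tested, and the final interval will come from the data. None of this reconciles 976 with 803 or brings 0.04 within the listed scenarios.

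**Conclusion.** The point holds in a narrow form. Two different numbers are called the minimum for the same study, neither is derived, and neither equals the planned 750. The 0.04 quoted with both lies outside the article's own planning scenarios for 500 patients. At 60–80% control the correct ranges, to two decimals, are 0.05–0.06 for 976 lesions and 0.06–0.07 for 803.

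The error is confined to the optimistic end: 0.050 instead of 0.04 for 976, and 0.055 instead of 0.04 for 803. Its effect is that the reduced study's best case appears better than the original target of 0.05, whereas at 80% control 976 lesions about equal that target and 803 fall short of it. The documents do not support the stronger conclusion that the sample is too small.

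This rests on precision meaning the full Wilson width, which the article's own 0.057 confirms, and on independent lesions. The widths for 976 are for treated lesions, before any drop-out.

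**What to change.** 1. State one planned lesion number with its derivation: 500 × 1.5 = 750, full width 0.057 at 80% control. Describe 976 as the number accrued, not as a minimum.
2. Say what 803 counts (for example evaluable lesions, if that is so) and how it was obtained, or remove it.
3. Restate the precision as 0.05–0.06 for 976 lesions and 0.06–0.07 for 803. Alternatively, if a 90% control rate was used, add it to the scenarios in the Sample size calculation section, with its basis.
4. Note that the precision for 976 lesions is before drop-outs as defined under Missing data. If a range after drop-out is given, state the assumed rate.

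The cost is a text correction. No further patients or data are needed. If the listed scenarios are kept, the quoted best case becomes slightly less favourable.
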